### Sample size

Anticholium® per Se is a pilot study precluding educated estimates. Primary results will be of great value in hypothesis generation. Thus, sample size was set for feasibility. With a number of 10 patients per treatment group and a sample size of 20 patients, a standardized effect (Cohen’s d) of 1.32 may be shown at a significance level of α = 5% with a power of 1 − β = 80%.

### Recruitment

All scheduled and all emergency admissions to the surgical clinic of the site are screened for inclusion and exclusion criteria. Patients operated on at the Surgical Clinic of the respective site who have to undergo subsequent surgery are repeatedly screened for inclusion and exclusion criteria. Between August 2003 and July 2008, the IOPIS handled 284 cases with intra-abdominal infection and sepsis, 206 of which had severe sepsis/septic shock [14]. In terms of figures, a little less than five patients with sepsis were thus cared for at IOPIS every month, a little more than three of which had severe sepsis/septic shock. Other clinical trials with similar eligibility criteria conducted by the Interdisciplinary Study Centre of the Departments of Anaesthesiology and Surgery, Surgical Clinic, Heidelberg University Hospital, during that period of time, were able to enrol approximately one subject every month.

## Methods: assignment of interventions

### Allocation

#### Sequence generation

For allocation of the participants, a randomization list was generated with SAS Proc Plan (SAS Institute Inc., Cary, NC, USA). The randomization sequence consists of unknown block sizes to balance the allocation of participants to groups if the trial is terminated before 20 participants have been reached. To further reduce biases due to other factors (apart from treatment) that may have changed over time [15], patients are treated according to the S-2 k guideline [16] of the German Sepsis Society (DSG) and German Interdisciplinary Association for Intensive Care and Emergency Medicine (DIVI). Block sizes are kept secret until unblinding.

#### Allocation concealment mechanism

The trial medication (verum and placebo) is prepacked in sequentially numbered containers according to the randomization list by [name] Köhler Chemie GmbH, the manufacturer. Participants are assigned order numbers and receive the medication in the corresponding containers.

#### Implementation

The randomization list was generated by the responsible biostatistician of the IMBI, who has no clinical involvement in the trial. Once the members of the study group have obtained informed consent, the investigator assigns the order numbers (patient number) and supplies the trial medication for application. However, participants are considered randomized with infusion of the initial dose.

### Blinding

The placebo has an identical pharmaceutical form and is externally indistinguishable when delivered, handled, e.g., drawn into the syringes, administered, or even spilled. The members of the study group are provided with ready-to-use, opaque 50-mL perfusor syringes with appropriate infusion lines containing the trial medication. The syringes handed to the members of the study group are labeled with the acronym Anticholium® per Se, EudraCT number, patient number, date of preparation, initials of the investigator or his representative, and the note Only for use within the clinical trial, and no other information, especially not for treatment group. The investigator and members of the study group, healthcare providers, data collectors, and participants are kept blinded during the clinical phase of the trial. To ensure blinding throughout the PK/PD study, plasma samples for the determination of physostigmine and eseroline plasma concentrations are immediately centrifuged, deep frozen, and stored at −70 °C until visit 16, to be analyzed later. The analyst is not involved in data acquisition with the respective patient any more. The assessment of cholinesterase activity is performed by a person not involved in further data acquisition from the respective patient.

Together with trial medication, the investigator is provided with a set of sealed envelopes, one per randomization number. These emergency envelopes contain information about the allocated intervention and may only be opened if it is medically indispensable to know what the participant has received. Once an envelope has been opened, date and reason must be documented and signed by the respective person. Whenever possible, the investigator is to consult with the deputy before unblinding.

## Methods: data collection, management, and analysis

### Data collection methods

All data collected in this trial will be recorded on standardized case report forms (CRF) which must ensure full documentation of all patient data required by the study protocol. Source data are available on worksheets or printed and diagnosed (e.g., electrocardiogram or laboratory results). The investigator is responsible for ensuring that all parts of the CRFs are filled in correctly. The CRFs are completed with pens, pencils are not allowed. Any change or correction to a CRF should be dated and initialed. Each CRF must be signed by the investigator at least once, the original is sent to the data management and a copy is retained at the study site.

### Data management

All protocol-required information collected during the trial must be entered by the investigator, or designated representative, in the case report form (CRF). The investigator, or designated representative, should complete the CRF pages as soon as possible after information is collected, preferably on the same day that a trial subject is seen for an examination, treatment, or any other trial procedure. Any outstanding entries must be completed immediately after the final examination. An explanation should be given for all missing data.

The completed CRF must be reviewed and signed by the investigator or by a designated sub-investigator. After keeping a copy at the trial center, the original CRF is sent to IMBI who is in charge of the data management within the trial.

In order to ensure that the database reproduces the CRFs correctly, the IMBI accomplishes a double entry of data to the statistical program SAS (SAS Institute, Inc., Cary, NC, USA). IMBI representatives will check completeness, validity, and plausibility of data using validating programs, which will generate queries. All validation rules will be predefined in a data validation plan. The investigator or the designated representatives are obliged to clarify or explain the queries. If no further corrections are to be made in the database it will be closed and used for statistical analysis. The data will be managed and analyzed according to the appropriate standard operation procedures (SOPs) valid in the IMBI.

According to section 13 of the GCP Ordinance [17], all important trial documents (e.g., CRFs) are archived for at least 10 years after completion of the clinical trial.

### Statistical methods

The primary endpoint is the mean SOFA score during treatment and subsequent intensive care of up to 14 days in the intention-to-treat (ITT) population. Anticholium® per Se being a pilot study missing values will not be imputed. The ITT population will include all randomized participants (full analysis population) from whom the primary outcome measure was obtained. The two-sided analysis of covariance (ANCOVA) model will include age as continuous covariate.

The per protocol population will consist of all participants from the ITT population without serious protocol violation. These include violations against eligibility criteria or departures from the treatment scheme, especially falling short of the minimum duration of administration. Exceeding the maximum duration of administration is not considered a serious protocol violation. Any interruption for > 90 min but ≤ 180 min and interruptions for source control of infection are not considered serious protocol violations, unless the continuous infusion is paused earlier than 90 min before the beginning or continued later than 90 min after the end of the intervention.

The χ2 test (categorical data) and further ANCOVA (continuous data) will be used for further descriptive analysis and secondary outcome measures, which will also be tabulated (measures of location and dispersion as appropriate for underlying empirical distribution). The Kaplan-Meier method and log-rank test will be used for survival analysis. Estimates of effect and 95% confidence intervals will be reported where possible and descriptive *P* values given. In addition, graphs are presented where possible.

Secondary analyses will include all participants from whom the primary outcome measure was obtained.

In the PK/PD study, plasma concentrations of physostigmine and eseroline are used to develop a population pharmacokinetic model for continuous intravenous administration. Possible structural models are examined and the impact of potential covariates (e.g., body weight, height, and gender) is investigated. Furthermore, PK/PD correlation of physostigmine concentrations and plasma cholinesterase activity is investigated.

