## Methods: participants, interventions, and outcomes

### Trial design

Anticholium® per Se is a prospective, randomized (1:1), double-blind, placebo-controlled, monocentric pilot study. Only patients with perioperative sepsis and septic shock as a result of intra-abdominal infection are eligible. Participants are randomly assigned to one group that receives physostigmine salicylate (verum group), or to the other group that receives 0.9% sodium chloride (placebo group). The treatment period is at most 5 days, and follow-up is limited to 90 days. The mean SOFA score (at least two individual values) during treatment and subsequent intensive care of up to 14 days is used as surrogate outcome (primary endpoint). Secondary outcome measures include 30- and 90-day mortality. An embedded PK/PD study investigates plasma concentrations of physostigmine and its metabolite eseroline.

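### The primary ANCOVA of absolute mean SOFA adjusts for age but not for baseline severity, so chance severity imbalance between two groups of 10 stays uncorrected and precision may be lost

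*Protocol article*

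**What the plan says.** All references are to the protocol article.

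- **Statistical methods** sets the endpoint: "The primary endpoint is the mean SOFA score during treatment and subsequent intensive care of up to 14 days in the intention-to-treat (ITT) population". This is a level during follow-up, not a change from baseline. The same section sets the model: "The two-sided analysis of covariance (ANCOVA) model will include age as continuous covariate". Age is the only covariate named, and no reason is given for choosing it.
- **Sample size** says the number was set for feasibility. "With a number of 10 patients per treatment group and a sample size of 20 patients", it states that "a standardized effect (Cohen’s d) of 1.32 may be shown at a significance level" of 5% with 80% power.
- **Trial design** describes a "prospective, randomized (1:1), double-blind, placebo-controlled, monocentric pilot study". **Sequence generation** describes blocks that keep group numbers balanced, and mentions no stratification by severity.
- **Eligibility criteria** (Table 1) requires an APACHE II score below 34, so that score is known before treatment.
- **Outcomes** lists measures covering the six SOFA organ systems: PaO2/FiO2, platelets, bilirubin, blood pressure and vasopressors, Glasgow Coma Scale and creatinine. The visit table is not reproduced in the text at hand, so it cannot be seen whether a SOFA score is recorded before the first dose.

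**The concern.** Because the outcome is an absolute score, a patient who enters with worse organ function will tend to have a higher mean SOFA whatever the treatment. Neither the randomisation as described nor the model takes entry severity into account. In a large trial this would cost only some efficiency. With 10 per arm, a chance difference in entry severity can be sizeable, and the age-adjusted difference would carry it into the reported estimate and confidence interval.

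In a hypothesis-generating pilot that estimate is the main product. A baseline severity covariate is the usual way to absorb such a difference, and at least one candidate is already collected.

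**Working it through.** **Inputs from the article.** 10 per group, N = 20, two-sided alpha 5%, power 80%, stated detectable effect d = 1.32, age as the single covariate.

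**Assumptions, because the documents give no figures.** r is the within-group correlation between baseline severity and mean SOFA, shown over a range. Severity is uncorrelated with age. Age is uncorrelated with the outcome unless stated.

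**1. The stated figure.** Two-sample t-test, noncentral t, 18 df, noncentrality d × √(10/2). The detectable effect at 80% power is 1.325, and power at d = 1.32 is 79.7%. The stated 1.32 is reproduced as an unadjusted two-sided t-test.

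**2. How large an imbalance chance produces.** The difference in mean baseline severity between two groups of 10 has SD √(2/10) = 0.447 in units of the baseline SD.
- Above 0.5 SD: 0.5/0.447 = 1.118, two-sided probability 26%.
- Above 0.75 SD: 9%.
- Above 1.0 SD: 2.5%.

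**3. What an imbalance does to the age-only estimate.** Shift = imbalance × r, in outcome SDs. For a 0.5 SD imbalance:
- r = 0.5: 0.25 SD, and 0.25/1.32 = 19% of the stated detectable effect.
- r = 0.7: 0.35 SD, and 0.35/1.32 = 27%.

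Simulation of the age-only model under no treatment effect (10,000 runs per setting) gave these rejection rates, conditional on the imbalance:

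| Imbalance (SD) | r = 0.5 | r = 0.7 |
|---|---|---|
| 0 | 2.3% | 0.7% |
| 0.5 | 5.0% | 5.0% |
| 0.75 | 9.3% | 11.0% |
| 1.0 | 15.1% | 24.2% |

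Rates below 5% when groups are balanced offset those above it when they are not.

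**4. What adding baseline severity gains or costs.** With k covariates, the variance of the treatment effect is proportional to (1 − R²) × [1 + k/(N − k − 3)]. The bracket is the average penalty for chance covariate imbalance.
- Age only: 1 + 1/16 = 1.0625, with 17 df.
- Age plus severity: (1 − r²) × (1 + 2/15) = (1 − r²) × 1.1333, with 16 df.
- Variance ratio: (1 − r²) × 1.1333/1.0625 = (1 − r²) × 1.0667.

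| Model | Variance vs age only | Detectable effect, 80% power (SD) | Power at d = 1.32 |
|---|---|---|---|
| Age only | reference | 1.370 | 77.0% |
| + severity, r = 0 | +7% | 1.421 | 74.0% |
| r = 0.2 | +2% | 1.392 | 75.7% |
| r = 0.3 | −3% | 1.355 | 77.9% |
| r = 0.5 | −20% | 1.231 | 85.2% |
| r = 0.6 | −32% | 1.137 | 90.2% |
| r = 0.7 | −46% | 1.015 | 95.4% |

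The variance breaks even where (1 − r²) × 1.0667 = 1, that is r² = 0.0625 and r = 0.25. Allowing also for the lost degree of freedom, the detectable effect breaks even at r of about 0.26.

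**5. Sensitivity.** If age itself has r = 0.2 with the outcome, the age-only detectable effect is 1.343. Adding severity gives 1.197, 1.101 and 0.974 at severity r = 0.5, 0.6 and 0.7, with variance changes of −21%, −33% and −48%. The picture is the same.

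**The case against.** The strongest reply is that the age-only ANCOVA is prespecified and valid, and that choosing covariates is an efficiency judgement in a pilot sized for feasibility. This stands as far as it goes: randomisation protects the estimate on average and the unconditional type I error. It does not answer the conditional problem in a single sample of 20.

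A second reply is that eligibility narrows severity (shock of under 24 hours, APACHE II below 34) and that averaging over up to 14 days weakens the link with one pre-dose value. Either could lower r. Below about 0.26 the extra covariate costs slightly more than it returns. This also stands, and is why the gain is given as a range.

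A third reply is that an unseen analysis plan may add covariates. However, the article states the primary model with age and nothing else, so a severity term would be an addition to a stated model.

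Some stronger readings are tempting but not supported:

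- **That most of the available precision is given up.** No correlation is documented. The variance is nearly halved only at r of about 0.7, and nothing is gained at 0.2.
- **That a severity imbalance is likely, or that it would dominate the result.** The chance of exceeding 0.5 SD is about one in four, and the resulting shift is 19 to 27% of the stated detectable effect at r = 0.5 to 0.7.
- **That the secondary analyses share the defect.** The article says only that "further ANCOVA (continuous data) will be used for further descriptive analysis and secondary outcome measures", which leaves their covariates and any transformation open. That is ordinary detail for an analysis plan that is not shown.
- **That a pre-dose SOFA contaminates the outcome mean.** The endpoint is defined as the mean during treatment and later intensive care, so the text shows no such error.

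**Conclusion.** The point holds as a matter of precision and conditional balance. The primary model names age alone, the outcome is an absolute score, and neither randomisation as described nor analysis accounts for entry severity. It is not a matter of bias or of an invalid test.

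Its size rests on the assumed r. If r is 0.5 to 0.7, adjustment would cut the variance of the treatment effect by about 20 to 46% and lower the detectable effect from 1.370 SD to between 1.231 and 1.015 SD. If r is below about 0.3, the change is a few per cent of variance in either direction, reaching +7% at r = 0. Because the possible gain is much larger than the possible loss, the change is worth making, but the documents do not establish that the gain will be large.

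**What to change.** Before unblinding, prespecify the primary ANCOVA with treatment, age and pre-dose SOFA as terms. Check the visit table and case report form for a pre-dose SOFA. If none is recorded, use APACHE II at enrolment. State that the pre-dose value serves only as a covariate and does not enter the outcome mean. The age-only model can be reported alongside as a sensitivity analysis.

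The article reports recruitment as ongoing, so on its own account the change can still be specified in advance. It would need to be documented as a change to the stated primary model. It needs no further patients, and no new data if APACHE II is used. The statistical cost is one residual degree of freedom (17 to 16) and, at worst (r = 0), a detectable effect of 1.421 instead of 1.370 SD, about 0.05 SD.

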### Interventions

Participants are enrolled within 24 h of onset of shock as defined in Table 1. Study medication is commenced within the following 2 h. The treatment group receives an infusion of 0.04 mg/kg physostigmine salicylate with a maximum dose of 4 mg. The infusion is administered at 0.4 mg/min (=1 mL/min = 60 mL/h). The initial dose is followed by a continuous infusion of 0.017 mg/min, i.e., 1 mg/h (=0.042 mL/min = 2.5 mL/h) for 2–5 days, i.e., 48–120 hours (treatment phase). The placebo group is treated with 0.9% sodium chloride.

The continuous infusion should not be interrupted; not even for surgery. If it is, the interruption is recorded in the case report form (CRF). Any interruption for > 90 min (five elimination half-lives > 18 min in humans) is considered a protocol violation, and the protocol violation is recorded in the CRF. Any interruption for > 180 min (ten elimination half-lives > 18 min in humans) is considered a discontinuation of trial medication. If the continuous infusion is interrupted for > 90 but < 180 min, the initial dose is repeated before the continuous infusion is resumed for the remaining time.

Criteria for discontinuing trial medication for an individual participant on the part of the investigator include occurrence of adverse events or delayed observation of violation of eligibility criteria that let it appear medically advisable.

The protocol does not make any provisions regarding interventions that are permitted or prohibited during the trial.

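### For source-control interruptions longer than 180 min, the treatment rule and the per-protocol rule conflict on whether the patient is discontinued or continues

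*Protocol article*

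**What the plan says.** Protocol article, Interventions. The general instruction is "The continuous infusion should not be interrupted; not even for surgery". Interruptions that happen anyway are recorded and graded by length:

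- Lower limit: "Any interruption for > 90 min (five elimination half-lives > 18 min in humans) is considered a protocol violation".
- Between the limits: "If the continuous infusion is interrupted for > 90 but < 180 min, the initial dose is repeated before the continuous infusion is resumed".
- Upper limit: "Any interruption for > 180 min (ten elimination half-lives > 18 min in humans) is considered a discontinuation of trial medication".

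This section makes no exception for surgery or source control, and gives no resumption rule at or above 180 min. The planned infusion time is 48 to 120 h.

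Protocol article, Statistical methods. "The per protocol population will consist of all participants from the ITT population without serious protocol violation". Serious violations are breaches of eligibility and departures from the treatment scheme, with too short an infusion named as the leading case. Two kinds of interruption are exempt. The first is any pause of more than 90 and up to and including 180 min. The second is the source-control pause: "interruptions for source control of infection are not considered serious protocol violations". This second exemption is lost if the pause begins more than 90 min ahead of the procedure, or if the infusion is restarted more than 90 min afterwards. Only the margin on each side of the procedure is limited, not the total length.

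**The concern.** Pauses of up to 90 min are not violations at all, and pauses of more than 90 up to 180 min are already exempt in their own right. The separate source-control clause therefore matters mainly for pauses longer than 180 min, which are the ones that Interventions counts as discontinuation.

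The disagreement goes beyond labels. By limiting how late the infusion may be continued after the procedure, the per-protocol clause presupposes that it is restarted. Interventions treats the same patient as having stopped. Two things therefore depend on which section is followed: whether the patient goes on receiving trial medication, and whether the patient counts in the per-protocol set. All participants have intra-abdominal infection with shock, and the article itself foresees surgery during the infusion, so the situation is within the scope that the rules were written for.

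**Working it through.** **Inputs.** From Interventions: violation above 90 min, discontinuation above 180 min, resumption between 90 and 180 min exclusive, minimum infusion 48 h. From Statistical methods: margins of 90 min before and 90 min after the procedure, no total cap. From Background: half-life 18–30 min. From Sample size: 10 patients per group, 20 in all.

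**The article's own figures.** The limits are given as five and ten half-lives of 18 min: 5 × 18 = 90 min and 10 × 18 = 180 min. Both reproduce.

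**Longest exempt source-control pause.** With a procedure of D min and the infusion off throughout, the maximum is 90 + D + 90 = 180 + D min. This exceeds 180 min for every D > 0. The article gives no procedure lengths, so these values of D are assumptions for illustration:

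| Assumed D (min) | Longest exempt pause (min) | Multiple of the 180-min limit |
|---|---|---|
| 60 | 240 | 1.33 |
| 120 | 300 | 1.67 |
| 180 | 360 | 2.00 |

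At 360 min the pause spans 360/30 = 12 to 360/18 = 20 half-lives. If the margins are not used at all, the pause exceeds 180 min only when D itself does.

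**The two sections side by side.**

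| Pause | Interventions | Statistical methods | Conflict? |
|---|---|---|---|
| Up to 90 min | Recorded, no violation | Not serious | No |
| Over 90, under 180 min | Violation; infusion resumed | Not serious | No |
| Exactly 180 min | Violation; neither resumable nor discontinued | Not serious | Gap at the boundary |
| Over 180 min, source control within margins | Discontinued; no resumption rule | Not serious; continuation presupposed | Yes |
| Over 180 min, other reason | Discontinued | Not exempt | No |

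**Consequence for the per-protocol set.** Take a source-control pause of more than 180 min, within the margins, before 48 h of infusion.

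1. If Interventions is followed, treatment ends there. The infusion is shorter than 48 h, and the patient is excluded for short duration.
2. If the infusion is restarted as Statistical methods implies and the patient reaches the minimum, the pause is exempt and the patient is retained.

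The same event gives opposite membership. If the pause comes after 48 h, the minimum has been met and membership need not differ, but whether the infusion restarts is still unresolved.

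**Weight of one patient.** 1/20 = 5% of the trial and 1/10 = 10% of an arm.

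**The case against.** The strongest reply is that discontinuation is a treatment status and serious violation an analysis label, so the two can differ without contradiction. Part of this stands. Interventions never says that discontinuation is a serious violation, and a patient discontinued after 48 h can properly be per protocol. A patient discontinued on day 1 could still be excluded under the minimum-duration criterion, because only the interruption is exempt and not a short infusion. It would therefore be wrong to say that the text keeps every such patient in the set.

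The reply fails on resumption. One section assumes that the infusion continues after source control; the other counts a long pause as the end of trial medication. Whether the minimum duration is met depends on which is followed.

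A reader might also see a contradiction between the instruction not to interrupt even for surgery and the existence of a source-control exemption. The text does not support that: the instruction is worded as a recommendation and is followed at once by rules for interruptions that occur.

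A reader might further infer that the per-protocol set could be settled after seeing results. The article does not show this. The study group is blinded during the clinical phase, and an analysis plan that is not shown may fix the classification beforehand. Such a plan could settle membership, but not a treatment rule that disagrees with it.

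**Conclusion.** The conflict is real and narrow. It covers source-control interruptions longer than 180 min that stay within the stated margins, plus a gap at exactly 180 min. It affects whether the infusion is resumed and, before 48 h, who belongs to the per-protocol set.

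The tempting inference that the main result is at risk does not hold. The primary endpoint is analysed in the intention-to-treat population, and secondary analyses use all participants with the primary outcome measured; neither population changes. The article defines a per-protocol set but names no analysis for it, and the trial is a hypothesis-generating pilot with descriptive P values.

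The number of patients concerned cannot be estimated, because the article gives no frequency of source-control procedures during infusion or of pauses for them. The 5% and 10% figures are the weight of one reclassified patient, not an expected effect. The result that the exempt pause can exceed 180 min for any procedure assumes that the full margins are used.

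**What to change.** 1. Reconcile Interventions and Statistical methods on whether a source-control interruption of more than 180 min is a discontinuation, and on how it counts towards the minimum duration and per-protocol membership. No view is taken here on which clinical rule is right.
2. Align the two sections at exactly 180 min.
3. Confirm that the case report form captures stop and start times. The article says only that the interruption is recorded.
4. Classify all interruptions under the reconciled rule before unblinding.
5. Report any per-protocol result with and without patients who had a single interruption longer than 180 min. Both sections set their limits per interruption, so no cumulative criterion is needed.

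The cost is amendment wording, which under Protocol amendments needs ethics committee and federal authority approval, and one sensitivity analysis. If stop and start times are not yet captured, a field must be added to the form. The article reports recruitment as incomplete, so at that stage an amendment was still possible.

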### Outcomes

The mean SOFA score (at least two individual values) during treatment and subsequent intensive care of up to 14 days is used as surrogate outcome in critically ill patients with perioperative sepsis and septic shock due to intra-abdominal infection.

Secondary measures include duration of artificial ventilation and intensive care, length of stay, 30- and 90-day mortality, arterial and central venous blood gas analyses, partial pressure of arterial oxygen/fraction of inspired oxygen (PaO_2_/FiO_2_), platelet count, leukocyte count, creatinine, urea, total bilirubin, C-reactive protein, prothrombin time, D-dimer, procalcitonin, IL-6, thrombin-antithrombin complex, mean blood pressure and use of vasopressors (frequency and duration), renal replacement therapy (frequency and duration), Glasgow Coma Scale (GCS) score, Acute Physiology And Chronic Health Evaluation (APACHE) II score, Simplified Acute Physiology Score (SAPS) II score, and the occurrence of side effects such as nausea or vomiting, clinically relevant changes in heart rate or blood pressure (mainly hypotension), and clinically relevant changes in airway resistance (mainly bronchiospasms as a result of hypersensitivity reactions to the sodium metabisulfite contained in the investigational medicinal product - spontaneous breathing: acute dyspnea or artificial ventilation: clinically relevant decline in respiratory volume at constant pressure settings, or clinically relevant incline in peak or inspiratory pressures at constant respiratory volumes).

Laboratory values, except IL-6 and thrombin-antithrombin complex, are determined during routine clinical examination in the inter-laboratory proficiency tested Central Laboratory (CL), or with a respective point-of-care device provided by the CL (for blood gas analyses). IL-6 and thrombin-antithrombin complex (from citrated plasma) are determined in the investigator’s laboratory using commercially available enzyme-linked immunosorbent assay (ELISA) kits. Moreover, additional serum samples are retained for further analyses at a later date.

Microbiological analyses of potential pathogens including susceptibility tests are performed at Heidelberg University Hospital, Department of Medical Microbiology.

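### Mortality, survival and the listed side effects are analysed only in patients with at least two SOFA values, so an early death can itself remove a patient from the mortality analysis

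*Protocol article*

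**What the plan says.** The Outcomes section of the protocol article defines the primary endpoint: "The mean SOFA score (at least two individual values) during treatment and subsequent intensive care of up to 14 days is used as surrogate outcome". Statistical methods adds that "missing values will not be imputed" and defines the main analysis set: "The ITT population will include all randomized participants (full analysis population) from whom the primary outcome measure was obtained". A later sentence in the same section carries the condition over to everything else: "Secondary analyses will include all participants from whom the primary outcome measure was obtained".

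The Outcomes section opens its secondary list with "Secondary measures include duration of artificial ventilation and intensive care, length of stay, 30- and 90-day mortality". The list ends with side effects: nausea or vomiting, and clinically relevant changes in heart rate, blood pressure and airway resistance. Kaplan-Meier curves and a log-rank test are named for survival, with no population of their own.

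Two other statements matter. Under Implementation, a participant counts as randomised once the initial dose is infused. Under Participant timeline, a patient who dies is recorded as leaving the ICU on the date of death, and that date goes into the case report form. For all others, the article says only that an attempt is made to establish 30- and 90-day vital status.

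**The concern.** Whether a patient has two SOFA values is settled after randomisation, and early death is one of the ways of not having them. Using that condition to select the population for a mortality analysis means that a patient must survive long enough to be scored before the death can count. The comparison is then no longer between the randomised groups, and it is distorted whenever early deaths or early ICU discharges differ between arms.

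The condition is defensible for the mean SOFA score, which cannot be computed without scores. It has no such justification for mortality, where the date of an ICU death is already known. With 10 patients per arm, each patient left out moves an arm's mortality by several percentage points. Because randomisation is tied to the start of the infusion, everyone left out has been exposed to trial medication, so the rule cannot be read as removing untreated patients.

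**Working it through.** **Step 1: the plan's own figure.** The Sample size section gives d = 1.32 for 10 per arm, two-sided 5% and 80% power. For a two-sample t-test with 18 degrees of freedom, the noncentrality is 1.32 × √(10 × 10 / 20) = 2.95. Power is 79.7%, and exactly 80% needs d = 1.325. The figure reproduces and is not in dispute. The point concerns who is analysed.

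**Step 2: the chain of definitions.**
- Primary outcome obtained = at least two SOFA values (Objectives, Trial design, Outcomes).
- ITT set = randomised and primary outcome obtained (Statistical methods).
- Secondary analyses = primary outcome obtained (Statistical methods).
- Mortality and side effects = secondary measures (Outcomes).
- The only other set, per protocol, is drawn from the ITT set, so it cannot restore anyone.

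It follows that a dosed patient with fewer than two SOFA values appears in no stated analysis of mortality, survival or listed side effects.

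**Step 3: effect on an arm's mortality.** With D deaths among n patients and k early deaths dropped, the arm reads (D − k)/(n − k). The change from D/n is −k(n − D)/[n(n − k)], a fall whenever anyone in the arm survives. Assume n = 10 and D = 6 in both arms, close to the 59% hospital mortality in septic shock that the Background section cites. The true difference is zero. Drop early deaths from one arm only:
- k = 1: 5/9 = 55.6% against 60%, a spurious benefit of 4.4 points.
- k = 2: 4/8 = 50.0% against 60%, a spurious benefit of 10.0 points.

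The opposite error is also possible. If one survivor who left the ICU early is dropped instead, the arm reads 6/9 = 66.7% against 60%.

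**Step 4: how likely is any loss?** The document gives no risk of having fewer than two SOFA values. For an assumed risk q per patient, the chance of losing at least one of 20 is 1 − (1 − q)^20:
- q = 2%: 33%, with 20 × 0.02 = 0.4 patients expected to be lost.
- q = 5%: 64%, with 1 expected.
- q = 10%: 88%, with 2 expected.

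These values of q are assumptions. The true value could be near zero.

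**The case against.** The best case for the plan is that this is a feasibility-sized, hypothesis-generating pilot with descriptive P values, that mortality is secondary, and that few patients, perhaps none, will lack two SOFA values. The SOFA schedule is in Table 2, whose content is not shown. If scoring starts at baseline and is daily, only deaths or discharges in roughly the first day are lost. The eligibility criteria also exclude APACHE II scores of 34 or more, a prognosis of death within follow-up and do-not-resuscitate orders. All of this limits the likely size. It does not rescue the rule, because the article states the population expressly and does not leave it to a fuller document. One could argue that secondary analyses means something other than analyses of the secondary measures, but that is not the natural reading.

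Several stronger conclusions are tempting and should not be drawn.

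- A reader might infer that early deaths and acute reactions disappear from the safety results altogether. The Harms section defines adverse events for patients given the treatment, records them all in the case report form and reports serious ones separately, with no SOFA condition. Only the side effects listed as secondary outcomes are caught.
- A reader might infer a known bias in favour of physostigmine. Nothing shows which arm would lose patients, or how many.
- A reader might infer a material loss of power. It falls to 74.8% at 9 per arm, and 69.0% at 8 per arm would need four patients lost, which nothing in the document supports. The sample size was in any case set for feasibility.
- A reader might infer that death under infusion before 48 hours counts as a serious violation, through "departures from the treatment scheme, especially falling short of the minimum duration of administration". The article does not say that death is such a departure, and the per-protocol set is supportive.

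**Conclusion.** The concern holds for mortality, for the survival analysis on the natural reading, and for the side effects listed as secondary outcomes. As written, the rule allows death to cause exclusion from the mortality analysis, and it calls a set ITT that need not contain every randomised patient. This should be corrected before analysis.

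The size cannot be fixed from the document. If one or two early deaths were lost from one arm, with the 6/10 mortality assumed above, the distortion would be about 4 to 10 percentage points. If every randomised patient has two SOFA values, it would be nil. The conclusion rests on the wording of the population rules and does not depend on the assumed counts.

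**What to change.** - Analyse 30- and 90-day mortality, Kaplan-Meier/log-rank and the listed side effects in all randomised participants, meaning everyone who started the initial dose, whatever SOFA data exist.
- Where later vital status cannot be established, censor the patient in the survival analysis at the last date known alive, and give the number of such patients by arm.
- Keep the two-value condition for the mean SOFA analysis only. Do not call that set ITT without qualification, and report the number excluded and the reasons by arm.

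This leaves the plan's decision not to impute SOFA values as it stands. The cost is a few sentences of text. ICU death dates and side effects are already collected, and the article describes the trial as still recruiting. The one drawback is that mortality denominators may differ from the SOFA denominator, which a footnote to the results tables can explain.
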